### 6.5.2 Statistics

Descriptive statistics will be calculated for general and clinical variables. Specifically, continuous variables will be summarised by their mean and SD, or median and interquartile range; categorical variables will be summarised as numbers and percentages.

The normality assumption will be tested with the Shapiro-Wilk test. Between-group comparisons will be carried out using either the two-sided unpaired t-test or the Wilcoxon two sided two-sample test for continuous variables depending on data distribution, and the chi-squared test for categorical variables. Correlations will be computed using Spearman's or Pearson's coefficients depending on data distribution.

Our primary end-point is the between-arm difference in T0 - T2 changes in CD-RISC 25 score.

Longitudinal changes will be analyzed using repeated measures hierarchical (patients nested in clusters) generalized linear mixed models, accounting for the cluster effect (using a random intercepts for clusters). To mitigate the potential risk of inflating the type I error in presence of a small number of clusters, we will use the Kenward-Roger degrees of freedom correction, which does not rely on the assumption of fixed cluster sizes [60].

All group comparisons will be carried out according to the intention-to-treat principle, i.e. participants will be analysed in the arm (READY for MS or relaxation) to which they were randomized. In addition, we will: carry out a per protocol analysis; assess the sensitivity of the results to excluding patients who missed three or more READY for MS group sessions. No interim analysis has been planned.

Inter-rater reliability will be assessed with the weighted kappa statistic for ordinal data, and the ICC for continuous data [61-63]; 95% confidence intervals (CIs) will be determined using the bootstrap method (1000 replications).

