## **4. ENDPOINTS**

### **4.1 Primary Endpoint**

Our primary end-point is the between-arm difference in T0 - T2 changes in CD-RISC 25 score.

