## 6.5 Data analysis

### 6.5.1 Sample size calculation

The sample size calculation was based on the results from the pilot study [paper under review], where we found a mean change in the CD-RISC 25 at 3-month follow-up in the READY for MS arm equal to 15.61 (standard deviation, SD: 13.63, n=18) vs. a mean change in the relaxation arm equal to 5.95 (SD: 14.11, n=19). Moreover, we estimated an intra-cluster correlation coefficient (ICC) equal to 0.08.

A sample size of 12 clusters per treatment arm (total number of clusters=24) with 10 individuals per cluster (total sample size 240) achieves 94.6% power to detect a mean difference of 9.66 between the two arms in terms of change in CD-RISC 25 at 3-month follow-up [59]. The SD of change in the CD-RISC 25 at 3-month is assumed equal to 14.53. The ICC is assumed, conservatively, equal to 0.10. The type I error (alpha) is assumed to 0.05.

Starting from the previous scenario (i.e. total sample size 240, 24 clusters, 10 subjects per cluster), we computed the study power assuming three scenarios of drop-out.

#### Scenario 1

Assuming a drop-out of 20% uniformly distributed among clusters (i.e. two individuals lost within each cluster): 12 clusters per treatment arm (total number of clusters=24) with eight individuals per cluster (total sample size 192) achieves 92.1% power to detect a mean difference of 9.66 between the two arms in terms of change in CD-RISC 25 at 3-month follow-up [59]. The SD of change in the CD-RISC 25 at 3-month is assumed equal to 14.53. The ICC is assumed, conservatively, equal to 0.10. The type I error ( $\alpha$ ) is assumed to 0.05.

#### Scenario 2

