#### *Analysis*

Longitudinal changes will be analyzed using repeated measures hierarchical (patients nested in clusters) generalized linear mixed models, accounting for the cluster effect (using a random intercepts for clusters).

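### If the primary mixed model is fitted to raw scores, its cluster intercept cancels from the T0–T2 contrast and drops the clustering of change used for power; the response is not defined

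*Protocol*

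**What the plan says.** The endpoint (section 4.1) is a difference in change: "Our primary end-point is the between-arm difference in T0 - T2 changes in CD-RISC 25 score". CD-RISC 25 is collected at T0, T1, T2 and T3 (section 6.2.5).

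Section 6.5.2 analyses longitudinal changes with repeated-measures "hierarchical (patients nested in clusters) generalized linear mixed models, accounting for the cluster effect (using a random intercepts for clusters"), and adds the Kenward-Roger correction to guard against type I error inflation with few clusters. It does not state the response variable, a cluster-by-time term, the within-patient covariance or any baseline adjustment.

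Section 6.5.1 powers the trial on change at three months. The design is given as "A sample size of 12 clusters per treatment arm (total number of clusters=24) with 10 individuals per cluster (total sample size 240"), and the protocol then states that this design "achieves 94.6% power to detect a mean difference of 9.66 between the two arms in terms of change in CD-RISC 25". It adds: "The SD of change in the CD-RISC 25 at 3-month is assumed equal to 14.53", and for the clustering: "The ICC is assumed, conservatively, equal to 0.10". The pilot value is given as 0.08 there ("we estimated an intra-cluster correlation coefficient (ICC) equal to 0.08") and as .07 in section 2.1.

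The ancillary CPDI analysis (section 7.1.3) uses the same model sentence, "accounting for the cluster effect (using a random intercepts for clusters"), without Kenward-Roger. CPDI is measured only at baseline and at three months.

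**The concern.** Both arms are delivered in groups, so people treated together may improve together. That shared effect arises after T0 and belongs to the change. A cluster intercept in a model of raw scores captures something else: stable differences in level between clusters. Section 6.3 makes such differences likely, because groups are assembled to be similar on CD-RISC 25. The fitted intercept variance could therefore look large, and clustering could seem dealt with, while clustering of change has no term in the model.

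At stake are the primary p-value and confidence interval. If the shared effect on change is left out, the standard error is too small and superiority would be claimed too often under the null.

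**Working it through.** **Inputs.** From section 6.5.1: k = 12 clusters per arm, m = 10 per cluster, difference 9.66, SD of change 14.53, ICC 0.10, alpha 0.05. The sides of the test are not stated there; two-sided is assumed, and it reproduces the stated power. Dropout leaves m = 8 (scenario 1) or a mean of 180/24 = 7.5 (scenario 3). Pilot ICC: 0.08 (section 6.5.1) or 0.07 (section 2.1).

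**Step 1: reproduce the stated power.** Design effect = 1 + (10 − 1) × 0.10 = 1.9. SE = 14.53 × √(2 × 1.9 / 120) = 2.586. A two-sided noncentral t with 22 df gives 94.6%, as stated. Scenario 1 (m = 8, design effect 1.7) gives 92.1%, as stated. Scenario 3 (m = 7.5) gives 91.3%, against 91.8% from the protocol's simulation. So the power calculation places the ICC on the change and tests it at cluster level.

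**Step 2: what a raw-score model does.** Write a patient's score at visit t as fixed effects + c (cluster) + p (patient) + e(t). Then score(T2) − score(T0) = fixed effects + e(T2) − e(T0). Both c and p cancel, so the contrast is tested as if changes were independent between patients: SE = 14.53 × √(2/120) = 1.876.

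If change does have ICC 0.10, its variance of 14.53² = 211.1 splits into 21.1 between and 190.0 within clusters. The true SE is √[2 × (21.1/12 + 190.0/120)] = 2.586. The model SE is too small by a factor of √1.9 = 1.38.

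**Step 3: type I error.** 2 × [1 − Φ(1.96/√design effect)]:

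| ICC of change | m | Design effect | Type I error |
|---|---|---|---|
| 0.10 | 10 | 1.90 | 15.5% |
| 0.10 | 8 | 1.70 | 13.3% |
| 0.10 | 7.5 | 1.65 | 12.7% |
| 0.08 | 10 | 1.72 | 13.5% |
| 0.08 | 8 | 1.56 | 11.7% |
| 0.07 | 10 | 1.63 | 12.5% |
| 0.07 | 7.5 | 1.455 | 10.4% |

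**Step 4: simulation** (20,000 null trials, 24 clusters of 10, ICC 0.10, the cluster effect on change equal at all post-baseline visits). The raw-score model with cluster and patient intercepts rejects 15.5% of the time with two visits and 16.4% with four. With change as the response and a cluster intercept, the rate is 4.8% (two visits). A test on cluster means gives 4.9%. With the effect of 9.66 added, the change-score analysis has 94.6% power.

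Actual mixed-model fits (120 trials, two visits) give a mean model SE of 1.87 for the cluster intercept alone, against an empirical SD of 2.69 for the estimate. Adding a cluster slope on time raises the mean SE to 2.58. Rejection rates in those fits were 20.8% and 9.2%. With only 120 trials they carry a Monte Carlo error of about 3 and 2 percentage points, so only the standard errors are relied on.

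**Step 5: Kenward-Roger.** The correction adjusts the standard error and df for the variance terms that are in the model; it cannot add one that is absent. With four visits, a patient intercept and independent errors, the contrast has (240 − 2) × 3 = 714 df, against 22 in the power calculation.

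**The case against.** The strongest reply is that the response may be change from baseline. The endpoints are defined as changes, section 6.5.2 speaks of longitudinal changes, and the power simulations draw one value of change per subject with the ICC on it. Kenward-Roger is there to handle few clusters, which has a purpose only if the primary contrast is tested at cluster level. With changes to T1, T2 and T3 as three repeated responses, a cluster intercept is the term that carries clustering of change, and all these parts fit together. The protocol does not say that the intercept is the only cluster term, and an analysis plan that is not shown may give the full structure.

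Much of this stands. The change-score reading is possible and would be valid, so a reader who infers that the protocol commits the trial to a 15% error rate goes further than the text. The text does not exclude the raw-score reading either, and the CPDI sentence points towards it. With only T0 and T2, a change score leaves one value per patient, and calling the model repeated-measures makes sense only if the two raw scores are the response. The same sentence for CD-RISC 25 most naturally means the same model. Nor is this only detail left for later, because the protocol names the cluster term, and one ordinary way of following its sentence gives an invalid test.

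It also stands that 15.5% needs both the ICC that the protocol calls conservative and full groups of 10. The pilot ICC comes from four groups and 39 participants, so the true value is uncertain; as it approaches zero the inflation disappears (4.9% in simulation at ICC 0).

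**Conclusion.** The point holds conditionally. Section 6.5.2 names a cluster random intercept and leaves the response undefined. If raw T0–T3 scores are modelled with that cluster term, the primary test omits the clustering of change on which the sample size rests. Type I error would be about 15.5% at the design values (16.4% in the four-visit simulation) and about 10–13.5% with the pilot ICC, the planned dropout, or both: two to three times nominal. If change from baseline is modelled, the error is near 5% and the plan agrees with its own power calculation.

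The figures assume a two-sided 5% test and the 24 clusters of section 6.5.1. The four-visit figure also assumes a patient intercept with otherwise independent errors. For CPDI the same argument applies more directly, but the documents give no SD or ICC from which to size it.

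**What to change.** State the primary model so that the cluster effect acts on change, and name one of these as primary:

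- change from baseline as the response, or post-baseline CD-RISC 25 adjusted for the T0 score, with a random cluster intercept; or
- raw T0–T3 scores with a random cluster-by-time term in addition to the cluster intercept.

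In each case use Kenward-Roger df and read the arm contrast at T2. These are alternatives, not the same analysis: the baseline-adjusted model estimates an adjusted difference, whereas the raw-score model estimates the difference in change given as the endpoint in section 4.1. The choice should therefore be made before the data are analysed. Use the same structure, with Kenward-Roger, for CPDI.

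The cost is a sentence or two of protocol or analysis-plan text, one variance component, and confidence intervals wider than those of the raw-score model with an intercept alone. The sample size already allows for that width, so the stated 94.6% power is unchanged, and no recruitment or assessment procedure is affected.

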#### Missing data

Sensitivity analyses will be performed if missing data will be present. The above mentioned statistical analyses will be re-run imputing missing data according to each of the following scenarios: 1) Baseline observation carried forward; 2) Last observation carried forward (LOCF); 3) Multiple imputation of multilevel data [64].

## **7. STRATEGIES FOR LIMITING COVID-19 IMPACTS ON THE STUDY**

Conducting a study that involves face-to-face group interventions during the COVID-19 pandemic exposes to the risk of having to abort interventions due to the emergence of local COVID-19 infection 'hot-spots'. The TSC carefully considered three options. First, pausing the study until the pandemic situation is under control. Due to the uncertainties of predictions about when the pandemic will be more manageable, this option was excluded. Second, delivering the interventions online. This option was also excluded because it would violate the MRC framework guidelines by nullifying the pilot RCT that, as purposed, provided data that informed the design of the present multi-centre RCT. Third, retaining the group delivery of both interventions with an option for teleconference delivery in the case of COVID-19 infection threats. This option was accepted by the TSC and involved the following set of actions.

- The study PI will have weekly contact with the participating centres in order to monitor changes in the local spread of COVID-19 and to take prompt infection control actions as necessary in accordance with guidelines from the Italian Government and local health authorities.
- In the case of one or more participating centres not being able to start the study up to four months after the commencement of enrolling participants in other centres, the TSC will propose the active centres to run the remaining groups in their place (competitive enrollment)
- If face-to-face group meetings are interrupted because of COVID-19 related-issues (e.g., local lockdown), all affected participants will be invited to complete their intervention via teleconferencing and the assessments completed as scheduled.
- Relevant COVID-19 information will be collected (i.e., COVID-19 infected; family member infected; COVID-19 impacts on employment; risk perceptions of COVID-19 infection because of MS; perceived additional burden of MS treatment/rehabilitation because of COVID-19).
- During data analysis a sensitivity analysis will be undertaken to explore any effects of the teleconference intervention delivery relative to the face-to-face delivery.

In addition to the strategies reported above, the Trial Steering Committee decided to run an ancillary study on the impact of the two interventions on the COVID-19 peritraumatic distress.

## **7.1 Ancillary study**

### 7.1.1 Aim

The aim of this ancillary study is to verify that participants in the Italian READY for MS would show higher improvements on the COVID-19 Peritraumatic Distress Index (CPDI) [65], compared to the control group (relaxation).

### 7.1.2 Endpoint

The primary endpoint will be the between-arm difference in T0 - T2 changes in CPDI score.

### 7.1.3 Methods

All the participants in the multi-centre RCT will be offered to participate in this ancillary study and asked to fill in the Italian version of the COVID-19 Peritraumatic Distress Index (CPDI) at baseline and 3-month follow-up (primary endpoint) [65].

#### *Measure*

The CPDI is composed of 24 items rated on a 5-point scale (0-4), measuring avoidance, compulsive behaviour, physical symptoms and loss of social functioning in the past week. A total score (0 – 100) is calculated by summing all item scores plus “4”, with higher scores indicating higher COVID-19 peritraumatic distress. A score below 28 indicates no distress, between 28 and 51 mild to moderate distress, and above 51 severe distress [66].

#### *Analysis*

Longitudinal changes will be analyzed using repeated measures hierarchical (patients nested in clusters) generalized linear mixed models, accounting for the cluster effect (using a random intercepts for clusters).

## **8. PANELS**

### **8.1 Trial Steering Committee (TSC)**

The TSC is the executive body for the trial. Members are [name], Dr. [name], Prof. [name], Prof. [name], and Dr. [name].

### **8.2 Independent Data and Safety Monitoring Committee (IDSMC)**

The IDSMC has been established to: (1) oversee the progress of the trial, and ensure that it is conducted, recorded, and reported in accordance with the protocol, GCP, and the applicable regulatory requirement(s); (2) monitor and supervise the progress of the trial, and the safety data. The IDSMC members will be a methodologist, a psychologist and an expert in complex intervention. Members are Prof. [name], Prof. [name], and [name].

The IDSMC is scheduled to meet (teleconference) at the end of the enrollment (by the end of October 2020 and by the end of February 2021), at the end of the intervention (by the end of January 2021, and by the end of April 2021), and at the end of the follow-up (June 2021, and October 2021), and depending on the needs of the trial. One week prior to each teleconference, the trial PI will send each IDSMC member a report with the following data (overall and by site, plus other information if needed): recruitment rates, reasons for exclusion, reason for drop out. The IDSMC should report in writing to the TSC, usually within 3 weeks after the teleconference.

### **8.3 Data Management and Analysis Committee (DMAC)**

The DMAC is responsible for data entry, quality assurance, and the statistical analyses.

The members are Dr. [name] (trial statistician), Dr. [name], [name], and Dr. [name].

### **8.4 Clinical Psychology Expert Panel**

An expert panel will oversee the program implementation and verify its fidelity. The members are [name], Prof. [name], Dr. [name] and Prof. [name].

## **9. PROJECT DURATION**

The project lasts 22 months (S6 Appendix – Multi\_READY for MS GANTT). Possible delays due to COVID-19 pandemic will be discussed with the funding source (FISM)

## **10. EXPECTED RESULTS AND IMPACT**

This study will produce evidence on the efficacy of a brief, structured group intervention to promote resilience in people with MS by comparing it with an active group intervention. It is expected that, by empowering participant inner resources, Italian READY for MS can promote a personal growth that may help participants to prevent or overcome difficulties in adjustment to MS, and to live a full and rich life. The Italian READY for MS program is brief and highly structured, which ease its affordability.

## **11. ETHICS AND ADMINISTRATIVE CONSIDERATIONS**

### **11.1 Ethical Considerations**

This clinical study was designed and shall be implemented and reported in accordance with the ICH Harmonized Guidelines for GCP, with applicable local regulations, and with the ethical principles laid down in the Declaration of Helsinki.

### **11.2 Ethics Committee Approval**

The protocol, Subject Information Sheet, Informed Consent Form and any advertisement for the recruitment of subjects must be reviewed and approved by an appropriately constituted Ethics Committee (EC), as required in chapter 3 of the ICH E6 Guideline. Written EC approval must be obtained by the Sponsor prior to shipment of study agent or subject enrolment.

### **11.3 Subject Information and Informed Consent**

Eligible subjects may only be included in the study after providing written (witnessed, where required by law or regulation), EC-approved informed consent, or, if incapable of doing so, after such consent has been provided by a legally acceptable representative of the subject. In cases where the subject's representative gives consent, the subject should be informed about the study to the extent possible given his/her understanding. If the subject is capable of doing so, he/she should indicate assent by personally signing and dating the written informed consent document or a separate assent form. Informed consent must be obtained before conducting any study-specific procedures (i.e. all of the procedures described in the protocol). The process of obtaining informed consent should be documented in the subject source documents. No study procedure can be performed before the written informed consent has been provided.

### **11.4 Confidentiality**

The investigator must ensure participant anonymity. On database and other documents, PwMS must not be identified by name but by patient number and initials. The investigator must keep a separate log of PwMS codes, dyad names and addresses, and signed informed consent forms, all of which must be kept strictly confidential.

Patient medical information obtained by this study is confidential and may only be disclosed to third parties as permitted by the Informed Consent Form (or separate authorization for use and disclosure of personal health information) signed by the patient, unless permitted or required by law. Medical information may be given to a patient's personal physician or other appropriate medical personnel responsible for the patient's welfare, for treatment purposes. Data generated by this study must be available for inspection upon request by representatives of the national and local health authorities, monitors, representatives, and collaborators, and the IRB/EC for each study site, as appropriate.

### **11.5 Protocol Amendments**

Any protocol amendments will be prepared by the PI. Protocol amendments will be submitted to the EC and to regulatory authorities in accordance with local regulatory requirements. Approval must be obtained from the EC and regulatory authorities (as locally required) before implementation of any changes, except for changes necessary to eliminate an immediate hazard to patients or changes that involve logistical or administrative aspects only (e.g. change in monitor or contact information).

## **12. STUDY MANAGEMENT AND MONITORING**

### **12.1 Protocol deviation**

Accidental or unintentional changes to, or non-compliance with the research protocol that does not increase risk or decrease benefit or; does not have a significant effect on the subject's rights, safety or welfare; and/or on the integrity of the data. Deviations may result from the action of the subject, researcher, or research staff. A deviation may be due to the research subject's non-adherence, or an unintentional change to or non-compliance with the research protocol on the part of a researcher. Examples of a deviation include: A rescheduled study visit; failure to collect an ancillary self-report questionnaire; subject's refusal to complete scheduled research activities.

### **12.2 Protocol Violation**

Accidental or unintentional change to or non-compliance with the Institute Research Board approved protocol without prior sponsor and Institute Research Board approval. Violations generally increase risk or decrease benefit, affects the subject's rights, safety, or welfare, or the integrity of the data. Examples of protocol violations: Failure to obtain valid informed consent (e.g., obtained informed consent on a non-date stamped form); accidental changes of the intervention program (Italian READY for MS or relaxation); not following inclusion/exclusion criteria.

